#### Electromyography

Surface electromyograms (EMGs) will be recorded using an eight-channel electromyography (EMG) device (New MiotoolUro Wireless; Porto Alegre, Brazil), 16-bit A/D converter, a sampling frequency rate fixed at 2000 Hz, automatic gain, safety isolation for 3000 V and common moderate (CMRR) of 126 dB. The signal will be filtered using a 20–500 Hz dual-pass Butterworth second-order digital filter. The preparation of the skin, sensor placement, and location preparation will be acquired according to the recommendation of the Surface Electromyography for the Non-Invasive Assessment of Muscles (SENIAM). Modified Glazer protocol will be used to verify muscle activity during rest-activity and fast and hold contractions. These protocols will be used twice, one only asking to increase abdominal pressure without conscious contraction of the pelvic floor and the second time only performing pelvic floor contractions.

### Laboratory data of maternal blood collection and analysis for biochemical analysis

Serum levels of relaxin, insulin, glucose, chemokine (C-C motif) ligand 7 (CCL7), calcium, calcitonin, parathyroid hormone (PTH), and vitamin D in maternal blood will be determined. The serum aliquots will be stored at − 80 °C for further batch processing according to the specific assay kit (relaxin: R & D Systems Catalog Number DRL200; Insulin: R&D Systems Catalog Number DINS00; and CCL7; R&D Systems Catalog Number DCC700). The total calcium levels (Catalog No. 448), calcitonin and PTH levels by the chemiluminescence method, vitamin D by high-performance liquid chromatography (HPLC) by following the procedures of processing and analysis of the manufacturer’s manual.

### RAM sample collection, storage, and laboratory assays

#### RAM sample collection

RAM samples will be collected according to a specific protocol. Morphological characterization, molecular analysis of muscle fiber function, ECM-related genes and proteins, gene and protein expression, OMICS, and ex-vivo assessment of RAM contractility will be performed according to specific protocols to characterize the hyperglycemic myopathy.

A biological sample of RAM from the region of a transverse Pfannenstiel incision will be obtained during C-section. RAMs are of mixed muscle fiber type [61, 62]. A 4 cm RAM tissue will be sampled in the lower portion. Dissections of skeletal muscle will be obtained within 10 min of delivery, dissected free from visible adipose and connective tissues, immediately divided into six fragments and stored according to different assays for further analysis.

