### Eligibility criteria

#### Inclusion criteria

Eligible participants are volunteer pregnant women with a GDM diagnosis between 24 and 28 weeks of pregnancy who have follow-up prenatal care at PDRC and C-section delivery. Subjects will be primigravida or second gravida women who underwent a planned C-section in their previous pregnancy, between 18 to 40 years old; with a singleton pregnancy and seen between February 2017 and March 2022.

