#### Exclusion criteria

Pregnant women aged < 18 years and > 40 years old, pre-pregnancy UI, known type 1 or type 2 diabetes mellitus, preterm delivery (< 37 weeks of gestation), multiple pregnancies, chronic arterial hypertension, pre-eclampsia, eclampsia, known fetal anomaly, urogenital cancer, high-risk pregnancy, multiple sclerosis, asthma, chronic sinusitis, ulcerative colitis, biliary cirrhosis, inflammatory bowel disease and/or anorectal surgery/ personal history of connective tissue disease, vaginal delivery or any clinical condition that may have jeopardized health status or the ability to provide written informed consent.

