#### Morphological assays

Part of the RAM will be harvested, powdered with talcum, frozen in liquid nitrogen and maintained at − 80 °C until processed by histochemical and immunohistochemical techniques for morphometric analysis and, to analyze the distribution, quantification, and characterization of key structural ECM components, such as type I and III collagens, the collagen type I/III ratio and GAGs. It will be examined via light microscopy and photographed. The morphometric analyses will be performed with Image-Pro Plus software (Version 7.0, Media Cybernetics, [name]) at Case Western Reserve University (OH). The proportions of RAM that fit each of the following types will be recorded: striated muscle, collagen, and blood vessel. Other samples (three samples/group) will be immersed in a fixative solution containing 0.1% ruthenium red, 3% glutaraldehyde, and 0.1 M cacodylate buffer for 12 h at 4 °C before transmission electron microscopy for ultrastructural analysis.

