### Statistical analysis

The mediator models assume that the predictor variable causes changes in the mediator variable, and the mediator variable then causes changes in the outcome variable. Mediation analysis will be conducted to evaluate whether the effect of GDM plus PS-UI on long-term UI is mediated through alteration in levels of all assessed parameters. The patient flow will be summarised using a diagram while social-demographic and obstetrics baseline characteristics will be reported as mean and standard deviation for continuous variables and count for categorical variables.

Multivariate logistic regression analyses will be conducted to identify the mediator variables and the outcome (UI 12-month C-section post-partum) that will be changed by the predictor variable (GDM plus PS-UI) as an independent variable after adjusting for confounders. Clinically important covariates will be investigated as potential confounders whenever appropriate for each outcome. There is likely to be missing data that will likely with the duration of the follow-up. The multiple imputations will be used to handle missing data [63]. Results will be expressed as odds ratio [OR], 95% confidence intervals and associated *p*-values. For all tests, the level of significance will be set at a p-value < 0.05. Assessment of the functional, morphological, biochemical, and molecular mediator variables are presented in Table 3.

**Table 3 Tab3:** Statistical tools will be used for the study

	Variables	Statistical methods
Clinical data		
Incidence of UI 12-month post-partum	Categorical	Multivariate analysis, odds ratio and 95% of the Confidence interval
ISI Questionnaire	Categorical	Chi-square test with corrections
PFM: Vaginal muscle contraction pressure; digital vaginal evaluation and US	Categorical	Chi-square test with corrections
RAM: US and Electromyography	Categorical	Chi-square test with corrections
Laboratorial data		
Comparison of serum concentration of CCL7; relaxin; calcium; parathyroid hormone; calcitonin; Vitamin D and Insulin	Continuous	Repeated Measures t-test or one-way analysis of variance (ANOVA) and Area under the curve
Laboratory assays of RAM sample		
Morphological assay Pathological, morphometric, immunohistochemical and ultrastructural	Continuous	ANOVA followed by Tukey’s multiple comparison tests for the normally distributed variables
	Categorical	Chi-square test with corrections

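### Previous C-section, present in every second gravida by the inclusion rule, is not a named covariate in the rectus muscle tissue analyses, although tissue is taken from the C-section incision region

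*Protocol article*

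**What the plan says.** **Who is sampled.** Inclusion criteria: "Subjects will be primigravida or second gravida women who underwent a planned C-section in their previous pregnancy". Previous C-section therefore coincides with gravidity: every second gravida has had one and no primigravida has. The Exclusion criteria do not remove a previous C-section; the nearest items are "anorectal surgery/ personal history of connective tissue disease".

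**Where the tissue comes from.** RAM sample collection: "A biological sample of RAM from the region of a transverse Pfannenstiel incision will be obtained during C-section". The same section places the sample in the lower portion of the muscle, has visible fat and connective tissue dissected away, and states that the assays serve to characterize hyperglycemic myopathy.

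**What is measured.** Morphological assays covers "key structural ECM components, such as type I and III collagens, the collagen type I/III ratio and GAGs", and adds: "The proportions of RAM that fit each of the following types will be recorded: striated muscle, collagen, and blood vessel". Other fragments go to extracellular matrix gene and protein expression, OMICS and ex-vivo contractility. Three samples per group go to electron microscopy.

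**How it is analysed.** For continuous morphology and gene expression, Table 3 gives ANOVA followed by Tukey's "multiple comparison tests for the normally distributed variables". Protein expression and contractility get a t-test or ANOVA with Tukey, and categorical morphology gets chi-square. No covariate is named in these rows. The Moderator variables section lists age, socio-economic status, education, ethnicity, body mass index, weight gain, nutrition and glycemic items, but not gravidity, parity or previous C-section. The Statistical analysis text says in general terms that clinically important covariates will be investigated as confounders where appropriate.

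**The concern.** The Background describes the signal seen in diabetic pregnant rats as more collagen, fibrosis and a higher type I/III ratio, and the study looks for the same in women. Repair after an earlier incision at or near the sampled site could plausibly move the same variables. The four cohorts are formed by observed GDM and PS-UI status at delivery, and nothing in the article matches or stratifies on previous C-section. An unequal share of second gravidae could then appear as a myopathy difference between cohorts.

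At stake are the secondary question on which mediators are abnormal, the secondary hypothesis that myopathy parameters mediate the association with incontinence at 12 months, and the aim of characterizing the muscle profile.

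**Working it through.** The plan gives no figure on this point, so there is none to reproduce. The structure follows from the sections above. The size can only be illustrated.

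**Inputs**
- n = 59 per cohort (Sample size). Tissue is taken at delivery, so later loss to follow-up does not reduce it. It is an upper figure, because RAM sampling needs a separate consent.
- Two-sided level 0.05 (Statistical analysis).
- Assumed: effect s of a previous C-section on a read-out, 0.5 to 1.0 within-stratum SD.
- Assumed: share previously operated, q1 v q0, in the two cohorts compared.
- No true GDM effect.

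**Formulas (normal approximation, one unadjusted comparison)**
- Bias b = s × (q1 − q0)
- Variance v = 1 + s² × [q1(1 − q1) + q0(1 − q0)] / 2
- Standard error = √(2v/n), and z = b / standard error
- Rejection rate = Φ(z − 1.96) + Φ(−z − 1.96)

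**Worked case, 60% v 40%**
- s = 0.5: b = 0.5 × 0.20 = 0.10. v = 1 + 0.25 × 0.24 = 1.06. Standard error = √(2.12/59) = 0.190. z = 0.53. Rate = 0.076 + 0.006 = 8.2%.
- s = 1.0: b = 0.20. v = 1 + 0.24 = 1.24. Standard error = √(2.48/59) = 0.205. z = 0.98. Rate = 0.162 + 0.002 = 16.4%.

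**Range over assumed shares**

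| Shares | s = 0.5 | s = 1.0 |
|---|---|---|
| 50% v 50% | 5.0% | 5.0% |
| 60% v 40% | 8.2% | 16.4% |
| 70% v 30% | 18.5% | 50.6% |

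With equal shares there is no bias. The SD rises to √1.0625 = 1.031 or √1.25 = 1.118, that is by about 3% or 12%.

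**Under the planned Tukey test.** I simulated four groups of 59, with both GDM cohorts at 60% and both non-GDM cohorts at 40%. A single GDM v non-GDM pair is rejected in about 2% (s = 0.5) to 6% (s = 1.0) of runs, against about 1% with equal shares. At least one false difference among the six pairs occurs in about 8% to 17%, against 5%. The per-pair rates are lower than in the table because Tukey corrects for multiplicity; the family-wise rates are close to the 59 v 59 figures.

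**The case against.** **The plan does provide for confounding.** Multivariate regression is to adjust for confounders, clinically important covariates will be investigated, and obstetric history and surgeries are collected. The moderator list is not a list of barred confounders. A reader might infer from Table 3 that every analysis of myopathy is unadjusted. The documents do not support that, since the mediation and regression analyses are described as adjusted. What stands against the objection is that the generic text does not change the tests that Table 3 names for tissue, and this factor is built into eligibility yet named nowhere.

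**Sampling detail is elsewhere.** The article refers to a specific collection protocol and to Additional file 1, which is not shown and may contain a rule on scarred tissue. This is a real limit. Removing visible connective tissue also reduces the problem, though it may leave fibrosis within the muscle.

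**The premise is not in the documents.** Nothing says that an earlier C-section alters the rectus muscle, that the earlier incision was a Pfannenstiel, or that gravidity differs by cohort. Nor can primigravidae be assumed to have unoperated muscle, since other abdominal surgery is not excluded. All of this stands, and it is why the numbers are an illustration. A reader might go further and infer that scar will produce a false myopathy finding, or might pool the GDM and non-GDM cohorts into a larger comparison with higher error rates. The documents support neither: the imbalance is unknown, and the design is of four cohorts.

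**Conclusion.** The point holds as a confounder that should be named in the tissue analyses. What is documented is the mix of previously operated and not previously operated women, the sampling region, the scar-sensitive read-outs, and tissue tests without a covariate. What is assumed is that earlier surgery affects the sampled muscle and that its share differs between cohorts. If both are true, the comparisons are confounded: about 8% to 16% false positives in one 59 v 59 comparison under the 60% v 40% illustration, and more under greater imbalance. If the shares are equal, the cost is a modest loss of precision. The point concerns the secondary tissue and mediator analyses. It would be a mistake to read it as a criticism of the primary comparison of incontinence at 12 months, which does not use the muscle samples.

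**What to change.** - In Table 3, replace ANOVA or t-test for continuous RAM read-outs with a linear model of cohort plus previous C-section (yes/no), with Tukey-adjusted contrasts between cohorts.
- For categorical RAM read-outs, replace chi-square with logistic regression or an analysis stratified by previous C-section.
- Add previous C-section to the DESeq design formula and to the mediation models.
- Report the share of previously operated women in each cohort, and repeat the tissue analyses in primigravidae only as a pre-specified sensitivity analysis.
- For the three electron-microscopy samples per group, keep previous C-section status the same or matched across groups, or report it for each sample. Three samples are too few to adjust.
- If Additional file 1 already has a rule on sampling near an earlier scar, refer to it in RAM sample collection.

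The cost is one degree of freedom per model and a sensitivity analysis that is less precise because it uses fewer women. The covariate comes from obstetric and surgical history already collected, so no new visits, samples or participants are needed.

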#### Morphological assays

Part of the RAM will be harvested, powdered with talcum, frozen in liquid nitrogen and maintained at − 80 °C until processed by histochemical and immunohistochemical techniques for morphometric analysis and, to analyze the distribution, quantification, and characterization of key structural ECM components, such as type I and III collagens, the collagen type I/III ratio and GAGs. It will be examined via light microscopy and photographed. The morphometric analyses will be performed with Image-Pro Plus software (Version 7.0, Media Cybernetics, [name]) at Case Western Reserve University (OH). The proportions of RAM that fit each of the following types will be recorded: striated muscle, collagen, and blood vessel. Other samples (three samples/group) will be immersed in a fixative solution containing 0.1% ruthenium red, 3% glutaraldehyde, and 0.1 M cacodylate buffer for 12 h at 4 °C before transmission electron microscopy for ultrastructural analysis.

### Sample size

It is not possible to calculate the sample size for Phase 1 of the recruitment. All eligible pregnant women will be invited to be included in this phase. Considering that the incidence of UI was higher at 24-months in GDM-positive C-section post-partum women (44.8%) as compared with women without GDM (18.4%) [5], assuming a two-sided confidence level of 95% and power of 80%, it will be necessary to follow-up 49 C-section post-partum women in each purposed cohort to identify at least a 22% difference between them. Considering a 20% loss in follow-up, we will include 59 women in each cohort, which means that 236 women will be included in this research.

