**Methods:**

The Diamater is an ongoing cohort study of four groups of 59 pregnant women each from the Perinatal Diabetes Research Centre (PDRC), Botucatu Medical School (FMB)-UNESP (São Paulo State University), Brazil. Diagnosis of GDM and PS-UI will be made at 24–26 weeks, with a follow-up at 34–38 weeks of gestation. Inclusion in the study will occur at the time of C-section, and patients will be followed at 24–48 h, 6 weeks and 6 and 12 months postpartum. Study groups will be classified as (1) GDM plus PS-UI; (2) GDM without PS-UI; (3) Non-GDM plus PS-UI; and (4) Non-GDM without PS-UI. We will analyze relationships between GDM, PS-UI and hyperglycemic myopathy at 12 months after C-section. The mediator variables to be evaluated include digital palpation, vaginal squeeze pressure, 3D pelvic floor ultrasound, and 3D RAM ultrasound. RAM samples obtained during C-section will be analyzed for ex-vivo contractility, morphological, molecular and OMICS profiles to further characterize the hyperglycemic myopathy. Additional variables to be evaluated include maternal age, socioeconomic status, educational level, ethnicity, body mass index, weight gain during pregnancy, quality of glycemic control and insulin therapy.

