#### Primary question

➣ Is the incidence of UI 12 months after C-section different in women who developed GDM plus PS-UI compared to women without these conditions?

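### 49 women per cohort give 80% power for the quoted 26.4-point gap in UI rates, not for the 22% difference that the sample-size section states

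*Protocol article*

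**What the plan says.** All of this stands in the Sample size section of the protocol article unless another place is named.

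- **Rates.** "the incidence of UI was higher at 24-months in GDM-positive C-section post-partum women (44.8"%), "as compared with women without GDM (18.4"%).
- **Error rates.** "assuming a two-sided confidence level of 95% and power of 80"%. The Statistical analysis section agrees: "For all tests, the level of significance will be set at a p-value < 0.05".
- **Result.** "it will be necessary to follow-up 49 C-section post-partum women in each purposed cohort to identify at least a 22% difference between them".
- **Enrolment.** With 20% loss to follow-up allowed for, 59 per cohort and 236 in total. The abstract's Methods paragraph likewise has "four groups of 59 pregnant women each", so any two cohorts compare 1:1.
- **Primary question** (section of that name): "Is the incidence of UI 12 months after C-section different in women who developed GDM plus PS-UI compared to women without these conditions".

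The section does not say which two rates the 22% lies between, or which two of the four cohorts are meant.

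**The concern.** One passage carries two effect sizes. The rates differ by 44.8 - 18.4 = 26.4 points, while the detectable difference is put at 22. At a given power, the sample size rises roughly with the inverse square of the difference. Moving from 26.4 to 22 points therefore multiplies it by about (26.4/22)² = 1.44, so a single n cannot serve both.

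This is the article's only sample-size justification. A reader who finds no significant difference at 12 months would believe that a true 22-point difference had only a 20% chance of being missed. Near the quoted rates, that chance is about one in three.

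A secondary matter is that the rates are for GDM versus no GDM at 24 months. The primary question compares GDM plus PS-UI with neither condition at 12 months. The power sentence does not say that it is meant for that contrast.

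**Working it through.** **Inputs.** Two-sided α = 0.05 (z = 1.960), power 80% (z = 0.8416), 1:1 comparison, 49 per cohort, and rates 0.448 and 0.184, all from the documents. The method is my assumption, because the article names none: the unadjusted comparison of two proportions with pooled variance under the null.

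With p̄ the mean of the two rates, d = p1 - p2, A = 1.960·√[2p̄(1-p̄)] and S = √[p1(1-p1) + p2(1-p2)]:

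- n per group = (A + 0.8416·S)² / d²
- power at n = Φ[(d·√n - A) / S]

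**Step 1: reproduce the plan's figure (44.8% v 18.4%).** p̄ = 0.316, A = 1.2886, S = 0.6304.

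- n = (1.2886 + 0.5306)² / 0.264² = 3.3096 / 0.0697 = 47.5, so 48.
- Power at 49 = Φ[(0.264×7 - 1.2886) / 0.6304] = Φ(0.887) = 81.3%. Exact enumeration of the chi-square test gives 81.4%.
- Other formulas give 45 (unpooled), 47 (arcsine) and 55 (continuity-corrected).

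So 49 and 80% belong to the 26.4-point gap.

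**Step 2: 22 points near the quoted rates.** Here d·√49 = 1.540 and d² = 0.0484.

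| Rates | A | S | Power at 49 | Exact chi-square | n for 80% |
|---|---|---|---|---|---|
| 40.4% v 18.4% (lower rate kept) | 1.2628 | 0.6252 | Φ(0.443) = 67.1% | 67.6% | 66.1, so 67 |
| 42.6% v 20.6% (centred) | 1.2886 | 0.6388 | Φ(0.393) = 65.3% | 65.4% | 68.9, so 69 |
| 44.8% v 22.8% (higher rate kept) | 1.3111 | 0.6506 | Φ(0.352) = 63.7% | 63.6% | 71.4, so 72 |

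The unpooled formula gives 66-69% power. A one-sided test, which the plan does not use, gives 75-78%.

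**Step 3: what 49 can detect.** The smallest difference with 80% power is about 26 points from either quoted rate. For 22 points, power at 49 is 77% at 32% v 10% and 80% at 30% v 8%. The lower rate therefore has to be about 8% or less.

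**Step 4: the plan's own attrition.** 59 × 0.80 = 47.2, so about 47 evaluable women per cohort, not 49. The 59 matches 49 × 1.2 = 58.8, whereas 49 / 0.80 = 61.25 would round up to 62. At 47, power is 79.6% for 44.8% v 18.4%. For 22 points it is 61.9% (44.8% v 22.8%) to 65.3% (40.4% v 18.4%).

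**The case against.** **The plan's figures agree apart from one.** The rates, α, power and 49 fit together, and only the 22% does not. It may be a slip for 26. This stands. A reader might infer that the stated power is wrong altogether, or that the study is underpowered. The documents do not support that, because at the only rates they quote, 49 per cohort does give 80%.

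**The 64-68% depends on rates that the plan does not name.** This also stands. The figure holds if one quoted rate is kept or the two are centred. A reader might take it as the power of the primary comparison, but the article gives no 12-month UI rate for women with neither condition. If that rate were as low as 8%, 22 points would have 80% power. The plan does not assume this, and the one comparator rate that it quotes is 18.4%.

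**Other groupings would have enough power.** One cohort against the other three pooled (49 v 147) has 83-86% power for 22 points, and all GDM against all non-GDM (98 v 98) has 91-93%. But the sentence counts 49 in each cohort and speaks of a difference between cohorts. Under the 49 v 147 reading, 42 to 46 women would be needed in the single cohort, so that reading does not explain the 49.

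**The source of the rates is disclosed.** It is: the section states the 24-month time point and the GDM split. Planning from the nearest published data is ordinary practice, so this part is a request for a clearer label and not an error.

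**Multiplicity.** Four cohorts and no named pair might suggest that power should be cut for six pairwise tests. The plan does not propose such testing for the primary outcome. It states one primary contrast.

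**Conclusion.** The point holds, limited to the 22% figure. The 49 per cohort and the 80% power follow from 44.8% v 18.4% (n = 48, power 81%). They do not follow for a 22-point difference near those rates, where power is about 64-68% and 67 to 72 per cohort would be needed. Either the 22% is mislabelled, or a 22-point target was never carried into n; the article does not show which.

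The result assumes an unadjusted two-sided 5% comparison of two cohorts of equal size, with rates kept at or centred on the quoted ones. The mismatch between the planning rates and the primary contrast is true but secondary.

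**What to change.** Reconcile the two figures in the Sample size section. If 26.4 points is what the design was built on, the sentence could read:

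> With 49 evaluable women per cohort, the power (two-sided 5%) is about 81% for 44.8% v 18.4%, a difference of 26.4 percentage points. For a difference of 22 points near these rates (40.4% v 18.4% to 44.8% v 22.8%) it is about 64-67%. If 20% of the 59 enrolled are lost, about 47 remain, and the power is about 80% and 62-65% respectively.

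Add that the calculation is for the single primary contrast, GDM plus PS-UI against neither condition at 12 months, and that its rates are borrowed from a comparison of GDM with no GDM at 24 months.

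If 22 points is the real target, the sponsor should say so, name the two rates, and acknowledge either the lower power or the need for 67 to 72 evaluable women per cohort.

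The restatement costs wording only. Enrolment stays at 59 per cohort and the analysis does not change. The stated detectable difference becomes less favourable.

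### Including 59 women per cohort does not keep the required 49 after a 20% loss: about 47 remain, and 59 covers only about 17% loss

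*Protocol article*

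**What the plan says.** All of the figures are in the Sample size section of the protocol article. The planning rates of urinary incontinence are 44.8% in women with GDM and 18.4% in women without it, taken from an earlier study at 24 months, with two-sided 5% significance and 80% power. From these the section concludes: "it will be necessary to follow-up 49 C-section post-partum women in each purposed cohort". It then adds the allowance for loss, "Considering a 20% loss in follow-up, we will include 59 women in each cohort", and the total, "which means that 236 women will be included in this research". The Methods paragraph of the abstract repeats the enrolment as "four groups of 59 pregnant women each", without the 20% or the 49.

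The wording fixes the role of each number: 49 is the count that must be followed up, and 59 is the count included before any loss.

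**The concern.** A loss to follow-up is a share of the women who were included. If 59 are included and one in five is lost, the number left should be at least 49, and it is not. The figure of 59 looks like 49 increased by a fifth, and adding a fifth does not offset losing a fifth of the larger number.

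At stake is whether the stated enrolment delivers the evaluable number on which the stated power rests. The primary question concerns incontinence at 12 months, the last scheduled visit, where cumulative loss will be greatest. The Statistical analysis section itself expects missing data. A reader of the article would take 59 per cohort as protecting 49 against a 20% loss.

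**Working it through.** **Inputs (all from the Sample size section):** rates 0.448 and 0.184; two-sided α = 0.05; power 80%; 49 per cohort to be followed up; 20% loss; 59 per cohort included; 236 in total.

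**1. The base figure of 49.** The pooled two-proportion formula without continuity correction is

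n = [z₀.₉₇₅·√(2p̄(1−p̄)) + z₀.₈₀·√(p₁(1−p₁)+p₂(1−p₂))]² / (p₁−p₂)²

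Here p̄ = (0.448 + 0.184)/2 = 0.316 and p₁ − p₂ = 0.264. The two square roots are 0.6575 and 0.6304. The result is n = 47.5, so 48 per cohort. The unpooled formula gives 44.8 (45) and the arcsine formula 46.7 (47); with a continuity correction the figure is 55. The stated 49 is within one woman of the pooled result, so I take it as given.

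**2. The enrolment of 59.**
- n × (1 + d): 49 × 1.20 = 58.8, rounded up to **59**. This matches the plan.
- n / (1 − d): 49 / 0.80 = 61.25, rounded up to **62**. This does not.
- Total: 4 × 59 = 236 as stated, against 4 × 62 = 248.

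The article prints no formula, so multiplication by 1.2 is an inference. Step 3 does not depend on it.

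**3. What 59 delivers.**
- Remaining after 20% loss: 59 × 0.80 = 47.2, about 47, two below 49.
- Losses that still leave 49: 59 − 49 = 10, and 10/59 = 16.9%.
- For comparison, 62 × 0.80 = 49.6, which meets 49, whereas 61 × 0.80 = 48.8 does not.

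The enrolment is therefore short by 62 − 59 = 3 per cohort, or 248 − 236 = 12 overall.

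**4. Effect on power at the plan's own rates.** The pooled form is

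power = Φ{[0.264·√n − 1.96 × 0.6575] / 0.6304}

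- n = 49: Φ(0.887) = 81.3%
- n = 47: Φ(0.827) = 79.6%

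The cost is 81.3 − 79.6 = 1.7 percentage points. With 47 women, the unpooled formula gives 81.9% and the arcsine formula 80.3%.

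**The case against.** The strongest reply is that the error hardly matters. The stated 49 carries a little slack over what the uncorrected formulas require (48, 45 or 47), and the loss step uses up little more than that. Whether 47 women fall below 80% power depends on a formula the article does not name: the pooled one says just below, the unpooled and arcsine ones say just above. The 20% is itself a planning guess with no stated basis, and 17% against 20% is within ordinary uncertainty. All of this stands, and it limits the weight of the point.

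A second reply is that multiple imputation is planned, so women lost to follow-up need not drop out of the analysis. This stands in part. However, the section sizes the study on women followed up, and imputing an outcome does not restore the full information of an observed one. It does not repair the sum.

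A third reply is that the abstract contains no separate error. That is right: it repeats 59 without the 49 or the 20% and contradicts nothing by itself.

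In the other direction, a reader might infer that the loss allowance leaves the study seriously underpowered, because the section also claims "to identify at least a 22% difference between them" and power for 22 points with 47 women is only 62% to 65%. The documents do not support blaming the loss step for that. With the full 49 women, power for 22 points is already only 64% to 67%. Nearly all of that shortfall comes from the mismatch between 22% and the gap of 44.8 − 18.4 = 26.4 points, which is a separate matter.

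**Conclusion.** The point holds as an arithmetic inconsistency within one paragraph. On its own figures, the stated enrolment does not yield the stated evaluable number under the stated loss, and nothing elsewhere in the article corrects this. The conclusion rests on reading 20% as a share of the women included, which is how the section words it, and on taking 49 as the requirement.

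The practical consequence is minor: power for the planned comparison moves from a little above its 80% target to roughly on it. This is a correction to a stated figure and does not call the design into question.

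**What to change.** Restate the allowance without changing enrolment, for example: 59 women per cohort retain 49 evaluable women with up to about 17% loss to follow-up; at 20% loss, about 47 remain. This costs only wording in the Sample size section. The 59 in the abstract can stay.

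If the sponsor prefers to keep both the 20% allowance and 49 evaluable women, the matching figures are 62 per cohort and 248 in total. The abstract would then change too, and 12 more women would be needed.

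In either case the edit should cover the loss allowance only. The stated detectable difference needs its own correction and should not be altered in passing here.
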